## Abstract

**Background:**

Catheter ablation of the pulmonary veins has become accepted as a standard therapeutic approach for symptomatic paroxysmal atrial fibrillation (AF). However, there is some evidence for an ablation associated (silent) stroke risk, lowering the hope to limit the stroke risk by restoration of rhythm over rate control in AF. The purpose of the prospective randomized single-center study "Mesh Ablator versus Cryoballoon Pulmonary Vein Ablation of Symptomatic Paroxysmal Atrial Fibrillation" (MACPAF) is to compare the efficacy and safety of two balloon based pulmonary vein ablation systems in patients with symptomatic paroxysmal AF.

**Methods/Design:**

Patients are randomized 1:1 for the Arctic Front^® ^or the HD Mesh Ablator^® ^catheter for left atrial catheter ablation (LACA). The predefined endpoints will be assessed by brain magnetic resonance imaging (MRI), neuro(psycho)logical tests and a subcutaneously implanted reveal recorder for AF detection. According to statistics 108 patients will be enrolled.

**Discussion:**

Findings from the MACPAF trial will help to balance the benefits and risks of LACA for symptomatic paroxysmal AF. Using serial brain MRIs might help to identify patients at risk for LACA-associated cerebral thromboembolism. Potential limitations of the study are the single-center design, the existence of a variety of LACA-catheters, the missing placebo-group and the impossibility to assess the primary endpoint in a blinded fashion.

**Trial registration:**

clinicaltrials.gov NCT01061931

## Background

About 20-37% of all ischemic strokes are of cardioembolic origin [1,2], caused by different cardiac disorders, but most commonly by atrial fibrillation (AF). The current demographic trends will lead to an increasing prevalence of AF [3,4] and implicate a growing risk of cardioembolic stroke [1]. In general, cardioembolic stroke has a worse prognosis and a higher recurrence rate than other ischemic stroke subtypes [5]. According to recent guidelines, the left atrial catheter ablation (LACA) of pulmonary veins (PV) is approved for treatment of symptomatic atrial fibrillation (AF) in patients with paroxysmal or persistent AF, refractory to antiarrhythmic medication [6]. Within the last years, LACA using radiofrequency has become a routine procedure and is widely used [7]. In patients with paroxysmal AF (<65 years) and without structural heart disease the achieved rate of persisting sinus rhythm is best and varies between 60% and 80% [8,9]. Major complications like pericardial tamponade, PV-stenosis, atrial-esophageal fistula, injury of the phrenic nerve and vascular damage by atrial and venous sheaths were detected more often in older patients (≥75 years) and patients with congestive heart failure [10]. Furthermore, there is some evidence for an ablation associated stroke risk [9,11,12], lowering the (so far) unproven hope to limit the AF-associated stroke risk by LACA. Considering that most AF patients "eligible" for LACA have a low stroke risk [13], the evident stroke rate of 0.4-1.1% in several registries [9-12] and a "silent" stroke rate of 10-11.3% [14,15] raise concerns and afford further investigation.

As demonstrated in humans, a balloon catheter using cryoenergy (Arctic Front^®^, Medtronic, Inc.) had safety advantages compared to radiofrequency devices [16]. Another basket shaped catheter device (HD Mesh ablator^®^, C.R. Bard, Inc.) combines circumferential mapping and radiofrequency delivery, leading to a reduced procedure and fluoroscopy time [17]. Both catheters are already used in daily clinical practice at the Department of Cardiology, Charité Campus Benjamin Franklin (CBF). Therefore, we designed a randomized single center study to evaluate the risks and benefits of LACA, using these innovative catheter devices.

Conducting MACPAF, we focus on the devices' periprocedural (silent) stroke rates and subsequent neuro(psycho)logical deficits. By using a highly standardized monitoring including serial brain magnetic resonance imaging (MRI) and neuro(psycho)logical tests we hope to set new standards for further trials in this regard. Furthermore, the implanted reveal recorder Reveal XT^® ^(Medtronic, Inc.) is highly accurate to detect clinically silent AF episodes, not infrequently occurring after LACA [18] on the one hand, and to determine the AF burden, on the other hand.

## Methods/Design

### Study population and study design

The Mesh Ablator versus Cryoballoon Pulmonary Vein Ablation of Symptomatic Paroxysmal Atrial Fibrillation (MACPAF) study is designed as a prospective randomized single center study conducted by the Department of Cardiology and Pneumology (Charité, CBF), the Center for Stroke Research Berlin and the Department of Neurology (Charité, CBF). The study has been approved by the local Ethics Committee (EA4/087/08) in February 2009. Randomization started in April 2009. Study entry and storage of data require subsequent consent by the patient. The inclusion and exclusion criteria are summarized in Table 1. Before undergoing LACA, patients receive an implantable device (Reveal XT^®^, Medtronic, Inc.) able to record the AF burden for at least 2 years. Within 24 h before LACA, all patients undergo transesophageal echocardiography (for exclusion of atrial thrombi), a brain MRI as well as a neuro(psycho)logical examination. A repeat brain MRI and neuro(psycho)logical examination will be performed within 48 h after the procedure. Patients will be randomized 1:1 for the cryoenergy device (Arctic Front^®^) or the newest device using conventional radiofrequency (HD Mesh ablator^®^). Before PV ablation, a CT image will be performed and segmented by CARTO Merge^® ^(Biosense Webster, Inc.) for visualization of PV anatomy. The LACA procedure will be performed by first introducing a ring shaped decapolar catheter via a single transseptal puncture. Afterwards, this catheter will be exchanged for the cryoballoon catheter or the mesh ablator, respectively. Finally, PV conduction will be re-evaluated by the decapolar catheter. In case of remaining PV conduction, the ablation procedure will be continued until isolation of all PVs is achieved. After transseptal puncture, heparin will be given to assure an activated clotting time of >300 s. Follow-ups will take place at 1, 3, 6, 9 and 12 months after LACA, including data acquisition from the Reveal XT^® ^or a 5-day-holter-ECG, respectively. Brain MRI and neuro(psycho)logical examination will be repeated after 6 months. The patient will be put on oral anticoagulation (INR 2-3) for at least 6 months after LACA to improve comparability of the results. The end of study is expected for late 2011.

**Table 1 T1:** MACPAF: Inclusion and exclusion criteria.

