### Aims and objectives

The primary objective of MACPAF is the efficacy of PV isolation, defined by achieving an exit block for all PVs per patient. We hypothesize that the cryoballoon catheter is more effective compared to the mesh ablator catheter in this regard. This is the only objective, which can not be assessed in a blinded fashion for the used ablation catheter. The secondary objective is the detection of LACA-associated (silent) cerebral thromboembolism by brain MRI and by neuro(psycho)logical examination. Further objectives are the determination of the AF recurrence rate after LACA using an implantable device, the detection of non-neurological major complications after LACA and the detection of (silent) cerebral thromboembolism within 6 months after LACA.

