### Sample size calculation and Statistical analysis

The primary endpoint for a patient is achieved when all four pulmonary veins are isolated. We hypothesize that corresponding to this primary endpoint the Arctic Front^®^ catheter is superior to the HD Mesh Ablator^®^ catheter. The null hypothesis of equal proportions of successful outcomes for both methods will be tested by the two-sided Fisher's exact test at significance level 0.05. Assuming a proportion of 75% successful ablations for the HD Mesh Ablation^®^ catheter, sample sizes of 54 for both treatment groups achieve 80% power to detect a 20% greater proportion of successes for the Arctic Front^®^ catheter. This corresponds to a proportion of 95% successful ablations for the Arctic Front^®^ catheter - a relative improvement of 27% for the Arctic Front^®^ catheter in comparison to the HD Mesh Ablator^®^ catheter.

An intention-to-treat analysis will be used to analyze treatment differences concerning predefined outcome measures. Treatment allocation will be done by gender-stratified randomization. For all outcome variables descriptive statistics will be collected. For quantitative traits, we will compute absolute and relative frequencies. In the case of continuous or quasi-continuous variables with nearly symmetric distribution, we will compute arithmetic mean, standard deviation, minimal and maximal values, otherwise median, quartiles, minimal and maximal values. Fisher's exact test will be used to compare proportions for dichotomous outcomes between independent groups or to test independency of two dichotomous traits within a population. Hypotheses about proportions for dichotomous outcomes within a single group (one sample analysis) will be tested by the binomial test. Assuming equal shaped distributions in the two treatment groups for at least ordinal scaled outcome variables group specific location parameters will be compared by the t-test or the Mann-Whitney test, respectively, depending on normality or non-normality of the distribution. Analysis regarding time to first AF-recurrence: Defining 'no observed AF-recurrence between 3 months after LACA and the end of follow-up' as 'survival', survival functions will be estimated by the Kaplan-Meier method. The null hypothesis of equal survival curves for the two treatment groups will be tested by the Log-Rank test.

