## Discussion

The pulmonary vein (PV) ablation in patients with symptomatic paroxysmal atrial fibrillation (AF) has received increasing attention over the last years and is now a well-established therapeutic approach to limit symptomatic paroxysmal AF [6,7]. The use of novel catheter techniques gives reasons to expect better safety and efficacy, but there is little clinical evidence so far [16,17]. Performing MACPAF, we hypothesize that the cryoenergy device (Arctic Front^®^) is superior to the balloon based device using radiofrequency (HD Mesh ablator^®^) with regard to efficacy and safety. Efficacy of LACA will be assessed by achieving a complete PV isolation as an acute effect, and by a lack of AF recurrence after a blanking period of three months (long-term efficacy), evaluated by an implantable device able to detect AF.

Focusing on the safety of LACA, the use of diffusion-weighted magnetic resonance imaging will precisely detect (silent) cerebral infarction, as recently demonstrated using a 1.5T MRI [15]. The use of a 3T MRI enables a higher resolution, improving the significance of stroke detection, while the detection of cerebral hemorrhage, chronic lesions and brain vessel occlusion is at least equal to 1.5T MRI [26]. Therefore, we expect a higher rate of silent strokes than the reported 10-11.3% [14,15]. Furthermore, the MACPAF study will demonstrate if the incidence of clinically silent or clinically evident strokes differs within the tested ablation systems. Moreover, a retrospective analysis of MACPAF might identify LACA procedure-independent risk factors, hopefully reducing LACA-associated stroke rate according to optimized technical conditions and patient selection. Using an implantable device for AF detection and a follow-up MRI after 6 months, we will be able to correlate the rate of (silent) strokes with the AF burden in patients on oral anticoagulation.

According to a http://www.clinicaltrial.org search, the MACPAF study meets highest technical standards. To eliminate potential conflicts of interest, this is an investigator-initiated clinical trial.

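### The rule for ending the procedure and the primary endpoint are the same state, and the endpoint's scoring point is not fixed, so the 75% versus 95% contrast may shrink by an unknown amount

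*Protocol article*

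**What the plan says.** All references are to the protocol article.

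- **Study population and study design.** After the assigned device has been used, "Finally, PV conduction will be re-evaluated by the decapolar catheter". The next sentence reads: "In case of remaining PV conduction, the ablation procedure will be continued until isolation of all PVs is achieved". No limit on time or attempts is given, and nothing is said about which catheter is used for the continuation.
- **Aims and objectives.** The primary objective is efficacy of PV isolation, "defined by achieving an exit block for all PVs per patient". The same section says this is the only objective that cannot be assessed blind to the catheter.
- **Sample size calculation and Statistical analysis.** "The primary endpoint for a patient is achieved when all four pulmonary veins are isolated". The test is the "two-sided Fisher's exact test at significance level 0.05". The mesh rate is set by "Assuming a proportion of 75% successful ablations" and the cryoballoon rate by "This corresponds to a proportion of 95% successful ablations", with 54 patients per arm and 80% power. Treatment comparisons follow intention-to-treat.
- **Discussion.** "Efficacy of LACA will be assessed by achieving a complete PV isolation as an acute effect", as distinct from freedom from AF recurrence after a three-month blanking period.

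**The concern.** The event that ends the procedure is the event that counts as success. If the endpoint is scored when the procedure ends, and the procedure ends only when all veins are isolated, every completed procedure is a success in both arms. The sample size section expects otherwise: about 13.5 of 54 mesh patients (25%) and 2.7 of 54 cryoballoon patients (5%) without full isolation. Taken literally, the two statements cannot both hold.

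Two features make the open scoring point matter more. Under intention-to-treat, isolation reached during continuation counts as a success for the assigned arm, however it was reached. And the operator, who knows the catheter, decides how long to go on, so effort could differ between arms. At stake are the size of the primary contrast, and with it the power, and how far the result reflects the catheter rather than persistence.

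**Working it through.** **Inputs from the protocol article:** 54 per arm; two-sided Fisher's exact test at 0.05; success rates 0.75 (mesh) and 0.95 (cryoballoon).

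**Method.** Power = Σₐ Σ_b Bin(a; 54, p₁) · Bin(b; 54, p₂) · 1[Fisher p(a, b) ≤ 0.05], summed over all possible success counts a and b.

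**Step 1: the plan's own figure.** With p₁ = 0.75 and p₂ = 0.95, power is 79.1% at 54 per arm and 80.1% at 55. The stated 54 per arm for 80% is reproduced to within rounding, so the arithmetic is not in question.

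**Step 2: effect of continuation.** Let f be the share of would-be failures that continued ablation turns into successes. The documents give no value for f. I assume that f is the same in both arms and, for this step, that 75% and 95% are the rates before continuation. Then

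p₁ = 0.75 + 0.25f, p₂ = 0.95 + 0.05f, difference = 0.20(1 − f).

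| f (assumed) | Mesh | Cryoballoon | Difference | Exact power, 54 per arm |
|---|---|---|---|---|
| 0 | 75.0% | 95.0% | 20 points | 79.1% |
| 0.25 | 81.3% | 96.3% | 15 points | 60.2% |
| 0.50 | 87.5% | 97.5% | 10 points | 34.1% |
| 0.75 | 93.8% | 98.8% | 5 points | 6.7% |
| 1 (literal rule) | 100% | 100% | 0 | 0% |

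The f = 0 row also gives the power if 75% and 95% are already final rates.

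**Step 3: how little rescue is needed.** Suppose all 54 cryoballoon patients succeed. With 48/54 mesh successes (88.9%), p = 0.027; with 49/54, p = 0.057. Significance therefore needs at least 6 mesh failures even in the case most favourable to the cryoballoon. Of the 13.5 failures expected, 13.5 − 6 = 7.5 is the most that continuation could remove before the test could no longer reach significance.

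**Step 4: the planned rates at another scoring point.** If the endpoint were scored before continuation and 75% and 95% turned out to be final rates, the earlier rates would be lower. With the 20-point gap kept (assumed rates), power at 54 per arm is 60% for 65% versus 85% and 55% for 60% versus 80%. Moving the scoring point therefore also requires a check of the planning rates.

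**The case against.** The continuation sentence states a procedural aim, and an aim does not guarantee its result. A device may fail to isolate a vein however long it is applied. By planning for 25% and 5% failures, the authors evidently did not expect universal success. On that reading a patient in whom the aim is not met is simply a failure, 75% and 95% are final rates, and no power is lost. The Discussion also ties the endpoint to the acute procedure, so it is not without any time point. The article names only the two study devices for ablation, and gives its success proportions by catheter, which suggests success with the assigned device. Finally, attempt limits and rules for ending unsuccessfully are details that a full protocol may hold and an article may omit.

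Much of this stands. It rules out the stronger reading that a reader might infer, namely that both arms must converge on 100% and the trial cannot answer its primary question. That follows only if continuation always succeeds, which the documents do not say. Nor do they say that other catheters are used for continuation.

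The objection does not remove the conflict. It works only if the continuation sentence is taken to mean less than it says. An acute effect fits both the first re-evaluation and the end of the procedure. And the point is not that detail is absent: the article states a rule and a set of planning rates that, as worded, exclude each other, and the scoring point is part of what the primary endpoint is.

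**Conclusion.** The concern holds in a limited form. The stopping criterion and the primary endpoint coincide, and the article fixes neither the moment of scoring (before or after continuation) nor a restriction to the randomised catheter. Read literally, the procedural rule contradicts the failure rates behind the sample size.

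The consequence ranges from no loss to total loss, and the documents do not say where in that range the trial lies. The 34% figure rests on the assumptions that half of the failures are converted, equally in both arms, and that 75% and 95% are rates before continuation. The 0% figure is the limit of the literal reading, not a forecast. The point still needs correction before analysis, because it concerns the definition of the primary endpoint in a comparison where the operator is unblinded.

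**What to change.** Leave clinical management as it is. Reconcile the wording in Study population and study design, Aims and objectives, Sample size calculation and Statistical analysis, and the Discussion, and state when and with which catheter the primary endpoint is scored, so that scoring does not coincide with the stopping rule.

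One measurement-only solution is to score isolation of all PVs, achieved with the randomised catheter alone, at the decapolar re-evaluation that is already performed, before any continued ablation. Patients not fully isolated at that point count as failures for the primary endpoint. Final isolation after continuation becomes a secondary outcome.

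This changes the question from final procedural success to success at the first check. The planning rates must therefore be confirmed for that scoring point and, if they do not apply, the power for 54 per arm restated.

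Cost: one extra case report form field; headline success rates that may look lower than final procedural success; and a stated power that may become less favourable.

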**Inclusion criteria**:
• Patients with ECG-documented symptomatic paroxysmal atrial fibrillation • At least one ineffective antiarrhythmic drug treatment • Age ≥ 18 and ≤ 75 years

**Exclusion criteria**

• Previous ablation procedure for AF • Cardiac surgery ≤ 3 months • Left atrial diameter > 50 mm or ejection fraction < 35% • Instable coronary artery disease or clinically relevant cardiac valve insufficiency • Hyperthyroidism, pregnancy or lactation • Coumadin or heparin intolerance • Concomitant disease with expected lifespan < 2 years • Contraindications for MRI • Acute cerebral infarction (DWI lesion) detected by brain MRI before LACA

### Aims and objectives

The primary objective of MACPAF is the efficacy of PV isolation, defined by achieving an exit block for all PVs per patient. We hypothesize that the cryoballoon catheter is more effective compared to the mesh ablator catheter in this regard. This is the only objective, which can not be assessed in a blinded fashion for the used ablation catheter. The secondary objective is the detection of LACA-associated (silent) cerebral thromboembolism by brain MRI and by neuro(psycho)logical examination. Further objectives are the determination of the AF recurrence rate after LACA using an implantable device, the detection of non-neurological major complications after LACA and the detection of (silent) cerebral thromboembolism within 6 months after LACA.

### Sample size calculation and Statistical analysis

The primary endpoint for a patient is achieved when all four pulmonary veins are isolated. We hypothesize that corresponding to this primary endpoint the Arctic Front^®^ catheter is superior to the HD Mesh Ablator^®^ catheter. The null hypothesis of equal proportions of successful outcomes for both methods will be tested by the two-sided Fisher's exact test at significance level 0.05. Assuming a proportion of 75% successful ablations for the HD Mesh Ablation^®^ catheter, sample sizes of 54 for both treatment groups achieve 80% power to detect a 20% greater proportion of successes for the Arctic Front^®^ catheter. This corresponds to a proportion of 95% successful ablations for the Arctic Front^®^ catheter - a relative improvement of 27% for the Arctic Front^®^ catheter in comparison to the HD Mesh Ablator^®^ catheter.

An intention-to-treat analysis will be used to analyze treatment differences concerning predefined outcome measures. Treatment allocation will be done by gender-stratified randomization. For all outcome variables descriptive statistics will be collected. For quantitative traits, we will compute absolute and relative frequencies. In the case of continuous or quasi-continuous variables with nearly symmetric distribution, we will compute arithmetic mean, standard deviation, minimal and maximal values, otherwise median, quartiles, minimal and maximal values. Fisher's exact test will be used to compare proportions for dichotomous outcomes between independent groups or to test independency of two dichotomous traits within a population. Hypotheses about proportions for dichotomous outcomes within a single group (one sample analysis) will be tested by the binomial test. Assuming equal shaped distributions in the two treatment groups for at least ordinal scaled outcome variables group specific location parameters will be compared by the t-test or the Mann-Whitney test, respectively, depending on normality or non-normality of the distribution. Analysis regarding time to first AF-recurrence: Defining 'no observed AF-recurrence between 3 months after LACA and the end of follow-up' as 'survival', survival functions will be estimated by the Kaplan-Meier method. The null hypothesis of equal survival curves for the two treatment groups will be tested by the Log-Rank test.

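### The Fisher's exact test chosen for the primary endpoint uses only about 1-3% of the 5% alpha at the expected success rates; another test would gain about 6-8 points of power on the same 108 patients

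*Protocol article*

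**What the plan says.** All of this stands in the Protocol article, mostly under 'Sample size calculation and Statistical analysis'.

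- The primary endpoint is binary per patient: all four pulmonary veins isolated. Equality of the two proportions "will be tested by the two-sided Fisher's exact test at significance level 0.05".
- The trial is sized for that test: "Assuming a proportion of 75% successful ablations for the HD Mesh Ablation" catheter, and a 20-point higher rate for the Arctic Front catheter ("This corresponds to a proportion of 95% successful ablations"). On these figures, "sample sizes of 54 for both treatment groups achieve 80% power". The abstract gives the total ("According to statistics 108 patients will be enrolled") and the 1:1 allocation.
- On allocation: "Treatment allocation will be done by gender-stratified randomization". Neither the primary test nor the time-to-recurrence test is described as using that factor; for the latter, "The null hypothesis of equal survival curves for the two treatment groups will be tested by the Log-Rank test".

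**The concern.** Fisher's test conditions on the total number of successes. With 54 per arm and few failures, the conditional distribution has only a few possible values, so the test usually cannot come close to 5% and stops well short of it. The unused alpha is lost power. A single-centre trial of 108 patients has little to spare, and the stated power sits right at its target with no margin.

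The choice can decide the result. With 51/54 against 44/54 successes (94% against 81%), Fisher's p is 0.073 and the trial is negative. An exact test that makes fuller use of the 5% rejects on the same data.

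The gender-stratified randomisation is a lesser matter. Analysing by the randomisation factor is usual practice and would cost nothing here, but how much it contributes has to be checked separately from the choice of test.

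**Working it through.** **Inputs from the article.** Success rates 0.75 (mesh) and 0.95 (cryoballoon); n = 54 per arm; two-sided alpha 0.05; Fisher's exact test.

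**Input assumed.** The gender split, which the article does not give: 35 men and 19 women per arm (70:38 overall). Splits from 50% to 70% men were also tried.

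**Method.** Let X and Y be the successes per arm, independent Binomial(54, p1) and Binomial(54, p2). For a test with rejection region R, sum over all 55 × 55 outcomes:

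P(reject) = Σ over (x, y) in R of b(x; 54, p1) × b(y; 54, p2)

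This is power at (0.75, 0.95) and true size when p1 = p2.

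**1. The plan's own figure.** With R = {Fisher p ≤ 0.05}, power at 54 per arm is 79.1%; at 55 per arm it is 80.1%. The stated 80% reproduces to within one patient per arm.

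**2. True size of Fisher's test at 54 per arm.**

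| Common success rate | True two-sided size |
|---|---|
| 75% | 2.9% |
| 80% | 2.7% |
| 85% | 2.5% |
| 90% | 1.9% |
| 95% | 0.85% |

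The maximum over all common rates is 3.3%.

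**3. Boschloo's test.** It uses Fisher's p as the ordering statistic and takes the largest cut-off c for which the size, maximised over the common rate, stays at or below 5%. Here c = 0.0743 and the maximum size is 4.96%. Because c is above 0.05, it rejects whenever Fisher's test does, and in further outcomes as well. The 51/54 against 44/54 example (p = 0.073) is one of these.

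**4. Power at 75% against 95%, 54 per arm.**

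| Test | Power | Difference from Fisher (points) | Size |
|---|---|---|---|
| Fisher | 79.1% | – | at most 3.3% |
| Boschloo | 85.5% | +6.4 | at most 4.96% |
| Pearson chi-square | 86.6% | +7.5 | at most 5.2% |
| Gender-stratified CMH, no continuity correction | about 86.6-86.8% | about +7.5 to +8 | about 4.5-5.1% (simulated) |
| Gender-stratified CMH, continuity-corrected | about 79% | about 0 | about 0.8-2.9% (simulated) |
| Exact stratified test | about 79% | about 0 | about 0.8-3.0% (simulated) |

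With Boschloo's test the chance of missing the planned effect falls from 20.9% (100 − 79.1) to 14.5% (100 − 85.5).

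**5. How much is due to stratifying?** Compare the uncorrected CMH test with the unstratified chi-square test (400,000 simulated trials, 35:19 split, overall rates held at 75% and 95%):

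| Assumed gender difference in success, mesh / cryo | CMH | Chi-square | Gain from stratifying |
|---|---|---|---|
| none | 86.7% | 86.6% | about 0 |
| 8 / 4 points | 87.0% | 86.7% | 0.3 points |
| 18 / 8 points | 88.0% | 87.0% | 1.0 point |

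The continuity-corrected CMH test stays at 79.0% with no gender effect and reaches 80.2% with the 18 / 8 difference. So the gain comes from dropping the conservatism, not from adding the stratum.

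**The case against.** The strongest reply is that nothing here is wrong. The article names Fisher's test and sizes the trial for that same test, so the conservatism is already paid for in the 54 per arm. Type I error is protected, and a familiar test with guaranteed size is a defensible choice when only about 3 failures are expected in the cryoballoon arm (0.05 × 54 = 2.7). That stands, and it rules out one tempting reading: that the trial is underpowered or its sample size miscalculated. The loss is relative to a better test, not to the stated 80%. It does not make Fisher's test the best choice, because Boschloo's test is also exact, also holds 5%, and is never less powerful.

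A reader might also infer that ignoring the gender stratum causes the power loss or invalidates the test. The article does not support either. It gives no gender split and no sign that gender predicts complete isolation. Leaving out the factor costs about 0-1 point under assumed effects and at most makes the test slightly more conservative.

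Finally, stratum adjustment and effect estimates are details that a condensed article may leave to an analysis plan that is not shown. That is fair for those details, but the primary test itself is fixed in the article.

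**Conclusion.** The point holds as an avoidable loss of efficiency. At the planned rates, Fisher's test gives up 6.4 points of power against Boschloo's test and about 7.5 to 8 against an uncorrected gender-stratified CMH test. The Fisher and Boschloo figures are full enumerations that use only the article's inputs. The CMH figures are simulated and rest on an assumed gender split, but hardly change for splits from 50% to 70% men. All of the power figures depend on the article's 75% and 95%.

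It is not a sample-size error and not a threat to validity, and the gender mismatch is a minor part of it. No power gain has been shown for stratifying the log-rank test, which serves one of the further objectives.

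**What to change.** Replace Fisher's test for the primary endpoint with one of these, named in full:

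- **Boschloo's unconditional exact test**, if guaranteed size is wanted (85.5% power, maximum size 4.96%). It does not use the gender stratum.
- **The gender-stratified CMH test, explicitly without continuity correction**, if the analysis is to follow the randomisation (about 86.6% power). It is asymptotic, with simulated size up to about 5.1%. The words on continuity correction are essential: with it, power stays at about 79-80% and nothing is gained.

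Restate the power for the chosen test; 54 per arm can stay. Stratifying the log-rank test by gender is optional, for consistency with the randomisation.

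The cost is analysis wording only: no extra patients, visits or data. The change should be fixed and dated before outcomes are compared by arm. This matters here because the primary endpoint is known at the procedure and, by the article's own account under 'Aims and objectives', cannot be assessed blind to the catheter.
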